## Abstract

**Background:**

Psychiatric patients are at high risk of becoming victim of a violent crime compared to the general population. Although most research has focused on patients with severe mental illness, depressed patients have been demonstrated to be prone to victimization as well. Victimization is associated with more severe symptomatology, decreased quality of life, and high risk of revictimization. Hence, there is a strong need for interventions that focus on preventing violent revictimization. Since emotion dysregulation is associated with both victimization and depression, we developed an internet-based Emotion Regulation Training (iERT) to reduce revictimization in depressed patients. This study aims to evaluate the clinical and cost-effectiveness of iERT added to Treatment As Usual (TAU) in reducing incidents of violent revictimization among depressed patients with a recent history of victimization. Furthermore, this study aims to examine secondary clinical outcomes, and moderators and mediators that may be associated with treatment outcomes.

**Methods:**

In a multicenter randomized controlled trial with parallel group design, patients with a major depressive disorder and a history of violent victimization over the past three years (*N* = 200) will be allocated to either TAU + iERT (*N* = 100) or TAU only (*N* = 100), based on computer-generated stratified block randomization. Assessments will take place at baseline, 8 weeks, 14 weeks, and 6 months after start of treatment, and 12, 24, and 36 months after baseline. The primary outcome measure is the total number of violent victimization incidents at 12 months after baseline, measured with the Safety Monitor: an adequate self-report questionnaire that assesses victimization over the preceding 12 months. Secondary outcome measures and mediators include emotion dysregulation and depressive symptomatology. An economic evaluation with the societal perspective will be performed alongside the trial.

**Discussion:**

This study is the first to examine the effectiveness of an intervention aimed at reducing violent revictimization in depressed patients. If effective, iERT can be implemented in mental health care, and contribute to the well-being of depressed patients. Furthermore, the results will provide insight into underlying mechanisms of revictimization.

**Trial registration:**

The study is registered at the Netherlands Trial Register (NTR5822). Date of registration: 4 April 2016.

## Background

Psychiatric patients are at high risk of becoming victim of a violent crime [1, 2]. Prevalence rates of violent victimization – commonly defined as physical assault, sexual assault or threat of violence – in psychiatric patients worldwide have been demonstrated to be up to 11 times higher in comparison with the general population, with most studies reporting 3 to 6-fold elevated odds [1–3]. Recently, a Dutch prevalence study conducted by Kamperman et al. (2014) [3] showed that 19.1% of outpatients with severe mental illness (SMI) had become victim of a violent crime over the past year, as compared to 6.1% of the general population. Whilst research has focused mainly on psychiatric patients as perpetrators (e.g., [4]), several studies have demonstrated that patients are more likely to be victim rather than perpetrator of a crime [5, 6].

Victimization is a highly stressful event that can aggravate existing symptoms [7] and substantially decrease quality of life [8] in psychiatric patients. Victimization is associated with physical injury, hospitalization [7, 8], treatment resistance [9], depression, posttraumatic stress disorder, and substance abuse [7]. Furthermore, initial victimization heightens the risk of future revictimization [10, 11], and therefore might induce a vicious cycle of stressful experiences and worsening symptoms. Due to increased service use, health care use, and productivity losses, victimization has a substantial economic impact as well [12].

To date, most studies have addressed victimization in patients with severe mental illness (SMI) [6, 13, 14] and patients with substance use disorders [15, 16]. Studies that specifically address victimization in other psychiatric populations, such as outpatients with affective disorders, are scarce. The only clinical study that focused on patients with depression revealed that depressed outpatients were 3.4 times more likely to be victim of a violent crime than members of the general population [17]. In a general population study of women, a current depression predicted subsequent physical victimization, but not subsequent sexual victimization [18]. Furthermore, a meta-analysis demonstrated depressed subjects to be vulnerable to domestic violence [19].

Despite the elevated prevalence rates and harmful consequences of victimization in psychiatric patients, evidence-based interventions specifically aimed at reducing victimization risk are not available. Currently, two interventions that aim to prevent victimization in patients with dual diagnosis [20] and psychotic disorders [21] are being examined in randomized controlled trials. There remains a strong need for evidence-based interventions that focus on reducing violent victimization in other high-risk psychiatric populations [3, 6, 13, 22], including depressed patients.

To be able to develop an intervention that specifically reduces victimization in depressed patients, knowledge regarding risk factors for victimization is necessary. Unfortunately, there remains a paucity of controlled, prospective studies that systematically examine risk factors, and no risk factors of victimization in depressed patients have yet been identified. Nevertheless, several – mainly cross-sectional – studies have identified various factors that have consistently been associated with victimization and revictimization in patients with SMI: symptom severity [2, 23], alcohol and drug abuse [2, 23, 24], a history of child abuse [23], and previous victimization [11]. In the general population, a history of child abuse [25], previous victimization [10], alcohol and drug abuse [26], and dysfunctional emotion regulation [27] have been associated with victimization risk.

Dysfunctional emotion regulation is considered to be both a consequence of prior victimization and a predictor of future revictimization [27, 28]. Emotion regulation refers to “the processes responsible for monitoring, evaluating, and modifying emotional reactions, especially their intensive and temporal features, to accomplish one’s goals” [29]. Using a prospective design, Messman-Moore, Ward and Zerubavel (2013) [27] demonstrated emotion dysregulation to significantly predict subsequent revictimization in previously victimized female students. Several authors hypothesize that dysfunctional emotion regulation interferes with the ability to appraise risk situations [30–32], and may therefore impede self-protection and escape responses. Comparably, Marx et al. (2005) [28] suggested that victims of child sexual abuse adapt certain emotion regulation strategies – especially passive, avoidant behaviors – to cope with their increased level of fear and arousal. However, instead of reducing their psychological distress, the authors hypothesized that these strategies (1) reduce the effort that can be given to self-protection in dangerous situations, (2) impair risk assessment and threat detection, and (3) signal vulnerability to possible perpetrators, thereby increasing proneness to future victimization [28]. Hence, dysfunctional emotion regulation may be an important target for preventing revictimization.

Over the past decades, emotion dysregulation has been pointed out repeatedly as a perpetuating factor of depression. Difficulties in regulating negative emotions are associated with depressive symptoms in both cross-sectional and longitudinal studies [33–36]. Correspondingly, evidence of experimental studies suggests that a current or past depression is likely to coincide with emotion dysregulation [37–40]. Changes in emotion regulation have been demonstrated to partially mediate treatment outcome in treatment for several disorders [41–43], including depression: Radkovsky et al. (2014) [35] demonstrated that the successful application of functional emotion regulation skills was associated with a reduction of depressive symptoms.

In conclusion, dysfunctional emotion regulation seems to be a promising target of intervention for both victimization and depression. Therefore, we developed an internet-based emotion regulation training (iERT) that will be added to Treatment As Usual (TAU). iERT is based on the Affect Regulation Training (ART) [44]: an intensive, structured group skills training that was demonstrated to be an effective addition to Cognitive Behavioral Therapy in decreasing depressive symptoms and enhancing various emotion regulation skills in depressed patients [45]. To provide an accessible and more feasible training that can be added to TAU, we developed a guided online version of ART that consists of 6 sessions. Numerous studies have demonstrated internet-based interventions to be an effective treatment for depression [46, 47]; moreover, interventions with online guided support have been found to be equally effective as face-to-face treatment [48, 49].

iERT is a transdiagnostic online add-on training that aims to enhance emotion regulation in patients by teaching them four emotion regulation skills: (1) non-judgmental awareness of emotions, (2) acceptance and tolerance of emotions, (3) analyzing emotions, and (4) modifying emotions. By enhancing emotion regulation skills, iERT aims to reduce violent victimization. Since both depressed patients and previously victimized patients are more likely to experience dysfunctional emotion regulation and have an increased revictimization risk compared to others, we will investigate the effectiveness of iERT in a high-risk population of previously victimized, depressed patients, who are specifically likely to benefit.

### Research aims

The main purpose of this study is to evaluate the clinical effectiveness of the addition of iERT to Treatment As Usual (TAU) in reducing incidents of revictimization among patients with a major depressive disorder and a recent history of victimization. Since previous studies underline the hypothesis that ER represents an underlying mechanism leading to revictimization, we expect TAU + iERT to significantly decrease incidents of revictimization as compared to TAU alone, by enhancing ER skills.

In addition, we aim to examine the cost-effectiveness of the addition of iERT to TAU in reducing revictimization, and its effectiveness in reducing depressive symptoms and other secondary clinical outcomes. We expect the addition of iERT to significantly reduce depressive symptoms and to improve other secondary outcomes. Finally, we aim to enhance knowledge regarding the underlying mechanisms of victimization. Using a randomized, prospective, and longitudinal design, we will therefore examine the relation between victimization and changes in a variety of relevant secondary outcomes and potential mediators and moderators.

## Methods

### Design

We will conduct a multicenter two-arm randomized controlled trial (RCT) with a parallel group design, in which 200 participants will be allocated to either TAU (*N* = 100) or TAU + iERT (*N* = 100) after the first baseline assessment. The effectiveness of the addition of iERT to TAU will be examined at 12 months after baseline assessment, and at follow-up 24 and 36 months after baseline assessment. Additional clinical outcome assessments will take place 8 weeks, 14 weeks, and 6 months after start of treatment. Apart from a diagnostic interview (Mini International Neuropsychiatric Interview; MINI) [50] that will be conducted at baseline and at 12 months follow-up, all assessments consist of self-report measures that will be completed over the Internet. The Medical Ethical Committee of the VU University Medical Center has approved the study protocol. The study is registered at the Netherlands Trial Register, part of the Dutch Cochrane Center (NTR5822).

### Participants

Our target population consists of 200 adult outpatients with both a depression and a recent history of victimization. Inclusion criteria are: (1) a diagnosis of a major depressive disorder according to DSM-IV criteria, with or without a concurrent anxiety disorder other than Obsessive-Compulsive Disorder; (2) an indication for evidence-based psychotherapy for MDD or anxiety disorder according to clinical practice guidelines; (3) having been victim of at least one violent crime (physical assault, sexual assault, or threat) over the past three years; (4) access to a computer or tablet with Internet connection; and (5) an age of 18 years or older. Exclusion criteria are: (1) insufficient understanding of the spoken and written Dutch language; (2) psychotic symptoms; (3) bipolar disorder; (4) concurrent substance dependency that requires intervention; and (5) current high risk for suicide that requires intervention.

### Sample size

Our primary outcome variable is the number of incidents of victimization (count data); therefore, a Poisson distribution is assumed. A priori sample size calculation was performed under this assumption, using the asypow package for R 3.0. Since we are the first to examine effects of an intervention aimed at reducing revictimization in depressed patients, it is difficult to determine an exact estimate of the effect size for the main outcome measure. We expect that patients in the experimental condition will have experienced 30% less incidents at the endpoint in comparison with patients in the control condition, which we consider a realistic and clinically meaningful effect.

A previous study showed that 34% of depressed patients had been victim of at least one violent crime during one year [17]. On average, these patients had been victim of 3.30 (SD = 4.32) violent crimes in a one-year period – after two outliers (2%) who reported an extremely high number of incidents were deleted. Based on these results, we calculated that the expected average number of incidents over a period of 12 months after baseline, in a subsample of recently victimized patients, will be 3.0. Since the observed variance in the previous study indicated an overdispersed Poisson distribution, we performed numerical simulation in R for our sample size calculation, with adjustment for the expected overdispersion. Based on this simulation, we will need a minimum of 95 patients in each condition to demonstrate a difference between conditions of 30% in total incidents with α = .05, two-sided, and 1-β = .80. To account for missing information due to patient dropout, we aim to include 200 patients in total.

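### The planning mean of 3.0 incidents is nearly the mean among same-year victims, yet it is applied to patients selected on any incident in three years, so it and the 80% power are optimistic

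*Protocol article*

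**What the plan says.** The Sample size section of the protocol article takes its planning values from one earlier study of depressed patients. It reports that "34% of depressed patients had been victim of at least one violent crime during one year" and continues: "On average, these patients had been victim of 3.30 (SD = 4.32) violent crimes in a one-year period", a figure obtained "after two outliers (2%) who reported an extremely high number of incidents were deleted". From these results it sets the expected count over the 12 months after baseline, "in a subsample of recently victimized patients, will be 3.0". The step from 3.30 to 3.0 is not shown.

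The assumed effect is that "patients in the experimental condition will have experienced 30% less incidents at the endpoint", tested at "α = .05, two-sided, and 1-β = .80". The simulation was run "with adjustment for the expected overdispersion" and gave a minimum of 95 per arm, raised to 200 in total for dropout.

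The Participants section defines the prior exposure needed for entry as "having been victim of at least one violent crime (physical assault, sexual assault, or threat) over the past three years". The primary outcome is the number of incidents reported at T4, covering the preceding 12 months.

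**The concern.** The source mean and the planning mean describe different groups. The 3.30 belongs to people with at least one incident in the year being counted. Trial patients are selected on an earlier and longer window, and nothing makes them victims again in the year that is counted. Some will report no incidents, and those zeros pull the mean down. A planning mean only 9% below the zero-free source mean leaves little room for them.

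The control-arm mean drives the amount of information in a count outcome. If it is too high, the 80% power claimed for 95 per arm is too high as well, even if overdispersion was handled correctly.

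**Working it through.** **Inputs** (Sample size and Participants sections): one-year prevalence 34%; mean 3.30 and SD 4.32; planning mean 3.0, taken here as the control-arm mean; rate ratio 0.70; two-sided alpha 0.05; power 80%; 95 per arm; entry on any incident in three years.

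**1. Which group the 3.30 describes.** If it were the mean over all patients, with 66% zeros, the SD could not be below 3.30 × √(0.66/0.34) = 4.60. The quoted SD is 4.32. So 3.30 is the mean among same-year victims, and the all-patient mean is 0.34 × 3.30 = 1.12.

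**2. What 3.0 implies.** 3.0/3.30 = 0.91. If revictimised patients average 3.30, then 91% of participants must be victimised again within 12 months.

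**3. A model favourable to the plan.** Let each patient have a fixed incident rate, gamma-distributed with shape k and mean m = 1.122, with Poisson counts each year. The chance of no incident in t years is P0(t) = (1 + t·m/k)^(−k). The expected next-year count among three-year victims is [m − e0·P0(3)]/[1 − P0(3)], with e0 = k/(k/m + 3). The share revictimised is [1 − P0(1) − P0(3) + P0(4)]/[1 − P0(3)].

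- Fitted to 34% prevalence: k = 0.239, three-year prevalence 48%, share revictimised 64%, 3.53 incidents each, mean **2.27**. For patients selected on one year only, the same fit gives 2.92.
- Fitted to the all-patient variance, 0.34 × (4.32² + 3.30²) − 1.122² = 8.79: k = 0.164, three-year prevalence 40%, share revictimised 66%, 4.19 incidents each, mean **2.76**. This fit gives a one-year prevalence of 29%, not 34%.

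Against these, 3.0 is too high by (3.0 − 2.76)/3.0 = 8% to (3.0 − 2.27)/3.0 = 24%. It roughly suits past-year victims, not the three-year window.

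**4. The plan's own n.** n = (1.960 + 0.842)² × V / (ln 0.70)², with (ln 0.70)² = 0.1272.

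- Plain Poisson: V = 1/3.0 + 1/2.1 = 0.810, n = 50.
- Quasi-Poisson with the source dispersion φ = 4.32²/3.30 = 5.66: n about 282.
- Negative binomial with α = (4.32² − 3.30)/3.30² = 1.41, V = 0.810 + 2α: n about 224.

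None of these gives 95. It is reached with φ = 1.90 or α = 0.365.

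**5. The mean alone.** Dispersion is held at those back-solved values and only the mean is lowered. Power = Φ(|ln 0.70|/√(V/95) − 1.96).

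| Control mean | Power, φ = 1.90 | Power, α = 0.365 | n per arm for 80% |
|---|---|---|---|
| 3.00 | 80% | 80% | 95 |
| 2.76 | 77% | 78% | 100-104 |
| 2.27 | 68% | 74% | 112-126 |
| 1.65 | 55% | 65% | 136-173 |

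The last row is an illustration: half the patients revictimised at 3.30 each.

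**6. Keeping the two problems apart.** With the source dispersion (φ = 5.66 or α = 1.41), power at 95 per arm is already 37-45% at a mean of 3.0. Lowering the mean to 2.27 takes it to 29-42%.

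**The case against.** The protocol's Background says that earlier victimization raises the risk of later victimization, so repeat victims may well have more than 3.30 incidents each. That stands. It means that 91% is not a requirement: at 4.19 incidents per revictimised patient, 3.0 needs only 3.0/4.19 = 72%. A reader might also divide 34% by 91%, get a ceiling of 37% on the three-year prevalence, and conclude that 3.0 is close to impossible. That bound rests on the same constant 3.30, so the protocol does not support it. Nor does it support treating years as independent (34% revictimised, mean 1.12), which contradicts the raised risk that it describes.

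The authors did go below 3.30, and an article condenses its calculations, so some allowance for zeros may be intended. But no figure that the article reports is a recurrence rate, and the favourable model, which already grants full persistence of risk and higher counts in repeat victims, still falls short of 3.0 for the three-year window. Restoring the two extreme reporters would raise the mean, but the Effectiveness section itself expects outliers to be removed.

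A reader might further attribute the fall to 37-45% power under the source SD to the planning mean. It appears with the mean at 3.0, so it is an overdispersion question and no part of this point.

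**Conclusion.** The point holds in direction and is moderate in size. The planning mean sits close to a zero-free mean from same-year victims, while the eligible population is defined by a three-year window and will contribute zeros. Under a stable-risk model fitted to the quoted figures, the expected mean is about 2.3 to 2.8, so 3.0 is optimistic by roughly 8 to 24%. That alone reduces power at 95 per arm from 80% to 77-78% or 68-74%, and to 55-65% if the mean were as low as 1.65.

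These figures assume that 3.0 is the control-arm mean, that individual risk is stable over time, and that dispersion is whatever makes 95 per arm correct at 3.0. The protocol gives no 12-month recurrence rate for three-year victims, so the true mean, and hence the exact loss, cannot be determined from it. This is an unsupported planning assumption, not a slip in arithmetic.

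**What to change.** In the Sample size section, replace 3.0 with a planning mean derived for the enrolled population: an assumed share revictimised within 12 months times an assumed number of incidents per revictimised patient, both stated with their basis. Show a range, for example means of about 1.65 to 3.0. Include the zeros in the variance, state the dispersion used, and give the power at 95 per arm, or the detectable rate ratio, across that range.

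Check the planning mean and variance against pooled, blinded Safety Monitor counts at T4 only. The T0 counts cover the 12 months before baseline, which lie inside the window used to select patients. They are inflated by that selection and could wrongly appear to confirm 3.0.

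The cost is a reworded paragraph and a blinded summary of data already scheduled for collection. The stated power becomes less favourable; no extra patients are needed.

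### At the only dispersion the protocol quotes, 95 patients per arm gives about 37–45% power for a 30% reduction in a comparison of arms at 12 months, not 80%

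*Protocol article*

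**What the plan says.** All of the planning figures are in the Sample size section of the protocol article.

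- Effect: the plan expects that "patients in the experimental condition will have experienced 30% less incidents at the endpoint in comparison with patients in the control condition".
- Control mean: the expected number of incidents over 12 months, "in a subsample of recently victimized patients, will be 3.0".
- Dispersion: "On average, these patients had been victim of 3.30 (SD = 4.32) violent crimes in a one-year period", and this was "after two outliers (2%) who reported an extremely high number of incidents were deleted".
- Method: "we performed numerical simulation in R for our sample size calculation, with adjustment for the expected overdispersion".
- Result: "we will need a minimum of 95 patients in each condition to demonstrate a difference between conditions of 30% in total incidents". This is stated for 80% power and a two-sided alpha of .05. The total is then raised to 200 to cover dropout.

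The section states neither the dispersion used in the simulation nor the test applied to the simulated data. The Primary outcome measure section sets the endpoint as the incident count at T4, and the Data analysis section plans a mixed model with a Poisson distribution.

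**The concern.** The section cites the earlier study's variance as its reason for adjusting, yet 95 per arm is less than twice what a pure Poisson outcome would need. A variance-to-mean ratio between 5 and 6 should raise the sample size several-fold. The printed inputs and the printed result therefore do not appear to belong together.

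This is the power statement for the primary outcome. If it is about double the true figure, a null result could be read as evidence against iERT when the trial was unlikely to detect its own target effect.

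**Working it through.** **Inputs, all from the Sample size section.** Control mean 3.0; rate ratio 0.70, so 2.1 in the iERT arm; two-sided alpha .05; power 80%; earlier-study mean 3.30 and SD 4.32. Allocation is 1:1 (Randomization and procedure).

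**Dispersion implied by the quoted SD.**
- Variance-to-mean ratio: 4.32² / 3.30 = 18.66 / 3.30 = 5.66.
- Negative binomial parameter: k = (18.66 − 3.30) / 3.30² = 1.41.

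**Formula.** Wald test on the log rate ratio: n per arm = (1.96 + 0.8416)² × V / (ln 0.7)² = 7.849 × V / 0.1272 = 61.7 × V.

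| Variance model | V | n per arm for 80% | Power at 95 per arm |
|---|---|---|---|
| Poisson | 1/3.0 + 1/2.1 = 0.810 | 50 | 97% |
| Negative binomial, k = 1.41 | 0.810 + 2 × 1.41 = 3.63 | 224 | 45% |
| Quasi-Poisson, ratio 5.66 | 5.66 × 0.810 = 4.58 | 282.5, so 283 | 37% |

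**Sensitivity.** Pairing SD 4.32 with the trial's own mean of 3.0 (a pair the protocol does not state) gives k = (18.66 − 3.0) / 9 = 1.74 and a ratio of 6.22. The requirement becomes 265 (negative binomial) or 311 (quasi-Poisson) per arm, with 39% and 34% power at 95.

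**Trying to reproduce 95.** Working backwards, 95 / 49.9 = 1.90, so 95 per arm corresponds to a variance-to-mean ratio of about 1.9, or an SD of √(1.9 × 3.0) ≈ 2.4 at a mean of 3.0. None of the two-sided calculations above on the quoted dispersion gives 95.

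One simulation of the T4 comparison does come close. In 20,000 runs at 95 per arm, with negative binomial counts:

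| Test | Rejection, 3.0 vs 2.1 | Rejection, true null |
|---|---|---|
| Unadjusted Poisson standard errors, k = 1.41 | 82% | 39–40% |
| Unadjusted Poisson standard errors, k = 1.74 | 80% | 43% |
| Robust standard errors, k = 1.41 | 46% | 6% |
| Robust standard errors, k = 1.74 | 40% | 6% |

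The unadjusted test returns the stated 80% but does not hold the stated alpha. The robust test roughly holds alpha, and its power agrees with the closed form.

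**Detectable effect at 95 per arm with 80% power.** Solving 7.849 × V(r) / 95 = (ln r)², with the second arm's mean set to 3.0r, gives r = 0.57 under the negative binomial with k = 1.41 (43% fewer incidents) and r = 0.51 under quasi-Poisson (49% fewer).

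**The case against.** **A pre–post mixed model could justify 95.** The Safety Monitor is also administered at baseline (Table 1), and the planned model is a mixed model. If each patient's underlying rate is the same before and after, apart from the treatment effect, a patient effect absorbs the between-patient overdispersion. The group-by-time contrast then needs 61.7 × (1/3.0 + 1/3.0 + 1/3.0 + 1/2.1) = 91 per arm. Simulation at 95 per arm gives about 81% power with type I error near 5%. So the unadjusted Poisson test is not the only route to the printed figure.

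This stands as a possibility but does not rescue the statement. The Sample size section describes a difference between arms at the endpoint and mentions no baseline counts. The route also depends on perfectly stable patient rates. With lognormal heterogeneity, type I error of that test rises to about 12–14% at a latent log-rate correlation of 0.9, and to 23–25% at 0.7.

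**The range depends on the distribution.** A Poisson-lognormal likelihood-ratio test at T4 only, with the same mean and variance, had about 49–54% power at 95 per arm (400 runs each, so roughly ±5 points), with type I error about 6%. A reader might infer that every valid analysis has 37–45% power. The documents do not support that: the range belongs to the negative binomial and quasi-Poisson comparisons. The lognormal figure is still well short of 80%.

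**The SD is borrowed.** It comes from the earlier study; no SD is given for this trial, and it is unclear whether 3.30 (4.32) describes all of those patients or only the victimized ones. But it is the only dispersion offered and the stated reason for the adjustment. If it covers victims only, adding patients with no incidents until the mean falls to 3.0 raises the ratio to about 6.0, which does not help. Further outlier removal does not explain the gap either, since 4.32 was computed after outliers had been deleted.

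**The simulation code is not shown.** An article may leave that detail to the full protocol, and its absence is not the complaint. The complaint is that the figures that are printed do not agree.

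**Conclusion.** The concern holds for a T4 comparison of arms with the quoted dispersion carried over. On that basis 95 per arm gives about 37–45% power for a 30% reduction at two-sided .05, and 80% power needs about 224 to 283 per arm, roughly 2.4 to 3 times the stated number.

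This rests on three assumptions: the earlier study's dispersion applies to this trial, the analysis uses no baseline counts, and the variance follows a negative binomial or quasi-Poisson form.

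A reader might also conclude that the authors generated overdispersed counts and then tested them with an ordinary Poisson model. The match to 80% makes that plausible, but it remains an inference, because neither the test nor the code is given and another route also arrives near 95. The main finding does not depend on it.

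**What to change.** Keep the total at 200 and restate the power, for example:

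> With 95 evaluable patients per arm, a T4 comparison that allows for overdispersion (SD 4.32) has about 37–45% power for a 30% reduction and 80% power for a reduction of about 43–49%, depending on the variance model.

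Then re-run the simulation with the exact primary analysis model. State the dispersion used and whether baseline counts enter, and report type I error next to power. If baseline counts or random patient effects are the basis for a higher figure, give the assumed within-patient correlation and show that alpha holds when patient rates are not perfectly stable.

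The cost is one simulation run and a rewritten paragraph. No extra patients are needed, but unless a justified use of baseline data supports more, the stated power becomes less favourable.
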